## Abstract

Radiation-free treatment for early-stage classic Hodgkin lymphoma (eHL) has been shown to be less effective than standard combined-modality treatment (CMT; chemotherapy plus involved-node radiotherapy (INRT)), which achieves long-term disease control of 94–95%. Approximately 70% of patients can be cured with chemotherapy alone, whereas about 5% fail CMT. Identifying patients who can safely receive chemotherapy alone and those requiring intensified CMT could enable a risk-adapted treatment strategy. The RAFTING trial (NCT04866654; EudraCT 2020-002382-33) is an international, prospective, phase 2, non-inferiority study enrolling patients 18–70 years, stage I–IIA eHL without bulky disease, B symptoms, or extranodal involvement. Low-risk (LR) patients are defined by total metabolic tumor volume (TMTV) <84 mL and negative PET-2. Those with at least one modified EORTC (mEORTC) risk factor, in which bulky disease is replaced by a large nodal mass (5–10 cm), receive four ABVD cycles, while those without risk factors receive two ABVD cycles alone. High-risk (HR) patients, defined by TMTV ≥84 mL and/or positive PET-2, receive “triple therapy”: 4 ABVD cycles, INRT (20/30 Gy), and nivolumab (240 mg q2w, ≤doses). LR patients are monitored using cfDNA. Limited relapse is treated with INRT (36 Gy) and nivolumab. The RAFTING trial is the first prospective eHL study to personalize treatment using TMTV and PET-2. It aims to omit radiotherapy in LR patients, intensify treatment in HR patients, and spare relapsed LR patients high-dose chemotherapy and autologous transplantation. CfDNA is being evaluated as a relapse marker. Despite the protocol’s complexity, this study exemplifies personalized medicine and could transform treatment practices.

## 1. Introduction

Patients with early-stage Hodgkin lymphoma (eHL) have a heterogeneous prognosis: approximately 60–70% can be cured with ABVD chemotherapy (doxorubicin, bleomycin, vinblastine, dacarbazine) (chemotherapy) alone, while 20–30% require combined modality treatment (CMT) with chemotherapy followed by involved-node radiotherapy (INRT). Despite an excellent treatment outcome after CMT, 5–10% of patients fail to achieve a cure due to disease progression or relapse [1]. Despite a high disease-specific survival rate (90–95%), the eHL treatment remains associated with a definite long-term treatment-related morbidity and mortality (TRM), resulting in impaired overall survival (OS) compared to an age- and sex-matched general population [2]. TRM includes complications related to both chemotherapy and radiotherapy (RT). Late effects, such as cardiovascular complications and secondary malignancies, are particularly associated with RT [3]. Despite a reduction of RT doses to 30 and 20 Gy, the use of modern conformal techniques, intensity-modulated RT, and precise 3D imaging for clinical target volume delineation, the risk of late RT-induced toxicity is still a concern [4]. Moreover, the TRM related to high-dose chemotherapy (HDCT) and autologous hematopoietic cell transplantation (auto-HCT) for disease rescue additionally affects long-term toxicity and survival of relapsed patients [5].

Previous studies of radiation-free treatment (RFT) in stage I–IIA HL patients with classic Hodgkin lymphoma without B symptoms and extra-nodal disease (eHL), the RAPID, H10, HD16 clinical trials, failed to demonstrate non-inferiority within margins of 7–10% [6,7,8]. However, in those trials, approximately 60–70% of patients were cured with chemotherapy alone. On the other hand, a small but non-negligible percentage of patients ultimately experience disease relapse after CMT. Therefore, an unmet need exists for a better stratification of eHL to tailor therapy according to individual disease risk, with the goal of preserving efficacy while minimizing RT-related TRM and with a better prognostic patient stratification to single out the small patient subset failing CMT. In these studies, cure with chemotherapy alone was achieved mainly in patients with negative interim positron emission tomography (PET) after the second chemotherapy cycle (PET-2). Conversely, approximately 25% of patients with a positive PET-2 (H10 trial) did not respond to standard CMT [7]. To date, PET-2 is regarded the strongest predictor of treatment failure not only in advanced disease but also in early-stage disease [7]. Classical bulky disease is a well-known unfavorable prognostic factor. Consistently, in a retrospective reappraisal of predictive factors for treatment outcome in the RAPID trial, a large nodal mass with the largest diameter ≥ 5 cm (LNM), measured on baseline contrast-enhanced computed tomography (CT), emerged as a strong predictor of treatment failure (HR 3.78, 95% CI 1.59–9.02; *p* = 0.003) [9]. The total metabolic tumor volume (TMTV) calculated on the PET/CT performed at baseline also proved to be of prognostic value in eHL, although different methods for TMTV computing have been proposed and different cut-off values have been adopted [10]. In patients enrolled in the standard arm of the H10 trial, a TMTV value > 147 mL indicated a risk of treatment failure 21% higher compared to that of patients with a lower value. [5]. However, in 129 non-bulky stage I–IIA patients from the French cohort of the H10 study, who matched the inclusion criteria of the RAFTING trial, a much lower value of 84 mL proved to be the most accurate threshold for predicting favorable treatment outcome. Patients with a TMTV value > 84 mL had a treatment failure rate of 44%, compared with 4% among patients with a lower value (unpublished observation, [name], personal communication, 2019). Finally, the H10 study showed that about 12.6% of RFT patients relapsed, and among them, 73% exclusively in the initially involved regions [7].

On the other hand, no data exist on the efficacy of RT rescue after first-line chemotherapy treatment alone. One of the older studies (from the 1990s) showed a 10-year disease-free survival in 30% of patients failing first-line chemotherapy and rescued with extended field radiotherapy [11].

Thirty years later, the monoclonal antibodies directed against the PD-1 immune checkpoint on T lymphocytes have demonstrated strong efficacy in both relapsed/refractory and untreated classic HL. When administered during or after INRT, anti-PD1 blockade may improve INRT efficacy through an abscopal effect and enhance a durable long-term disease control in high-risk patients [12,13].

Based on these data, the RAFTING trial was designed to verify a risk-adapted therapeutic strategy for stratifying eHL patients with favorable (I–IIA nonbulky) disease into low-risk (LR) patients who could be safely treated with chemotherapy alone, without consolidation radiotherapy, and high-risk (HR) patients, who would benefit from standard CMT followed by the anti-PD1 monoclonal antibody nivolumab. The study was also aimed to determine whether the association of RT and nivolumab could rescue LR patients failing chemotherapy with the criteria of “limited relapse” (see below). Thus, the study intends to preserve a high efficacy of the proposed overall therapeutic strategy, while reducing treatment-related toxicity and long-term morbidity.

## 2. Methods and Analysis

### 2.1. Study Design

The RAFTING trial (NCT04866654, EudraCT 2020-002382-33) is a prospective, multicenter, international (Poland, Italy, Spain), single-arm, non-inferiority, phase 2 study.

### 2.2. Enrolled Population

Untreated, favorable stage I–IIA with histologically confirmed classical eHL according to the current World Health Organization (WHO) classification, aged 18–70, without classical bulky (>10 cm), B symptoms, or extranodal disease are eligible for study enrollment. Other inclusion/exclusion criteria are standard for prospective onco-hematological studies.

### 2.3. Patient Stratification and Treatment

Stratification is performed in two steps to define the low- and high-risk categories.

The first is based on the TMTV value at baseline (low or high) and presence/absence of modified EORTC (mEORTC) criteria, in which the classical bulky disease (defined as a nodal mass larger than 10 cm) is replaced by a “large nodal mass” (LNM) of 5–10 cm in diameter (Figure 1). The second step is after the second chemotherapy cycle and is based on PET-2 results.

The low-risk (LR) group is defined by a baseline TMTV < 84 mL and negative interim PET-2 (Deauville scale; DS: 1–3). Within this category, patients are further split into two more categories: group 1a—patients without mEORTC risk factors that receive two chemotherapy cycles only, and group 1b—patients with at least one risk factor according to the mEORTC criteria that receive four chemotherapy cycles (Figure 2). The ABVD chemotherapy includes doxorubicin 25 mg/m^2^, bleomycin 10 IU/m^2^, vinblastine 6 mg/m^2^, and dacarbazine 375 mg/m^2^, administered intravenously on days 1 and 15 of each 28-day cycle.

The HR group includes patients with either a positive PET-2 (DS 4–5, group 3a) and/or baseline TMTV ≥ 84 mL (group 3b). Both patient subsets receive a “triple therapy,” consisting of four chemotherapy cycles, INRT at either 20 or 30 Gy depending on the absence or presence of baseline mEORTC risk factors, respectively, followed by Nivolumab maintenance administered every two weeks at a dose of 240 mg intravenously over 30 min for up to one year, for a maximum of 24 doses (Figure 2). This duration was selected based on the CheckMate 205 and KEYNOTE-087 studies [12,13]. The newly diagnosed advanced-stage HL patients (CheckMate 205 study, group D) received up to 16 doses of nivolumab (4 doses of monotherapy and 12 in combination with AVD chemotherapy). The relapsed/refractory patients received nivolumab up to disease progression or unacceptable toxicity, with a possibility of treatment discontinuation in group C for patients with CR for 1 year. In both cases, acceptable CR rate and duration were achieved. The KEYNOTE-087 data show that 1 year of PD-1 blockade is associated with sustained remissions [14]. Recognizing that the optimal duration of anti-PD-1 therapy in this setting remains unknown, this study will explore correlations between treatment duration, toxicity, and outcomes to inform future trials.

In the LR group, two different patterns of disease relapse are defined (limited and extended relapse). Limited relapse is characterized by nodal recurrence in the initially involved regions, with or without a maximum of three new nodal sites, and absence of B symptoms, which allows the use of INRT as rescue and does not exceed the field of radiation therapy. The consistency of each relapse with the predefined criteria of limited relapse was assessed by a panel of PET reviewers and a medical monitor. Limited relapses are treated with INRT at 36 Gy followed by nivolumab according to the same schedule applied in the HR groups (group 2).

Patients requiring RT according to the study protocol received INRT within 4–6 weeks after completion of chemotherapy. The RT techniques and safety constraints followed the guidelines of the International Lymphoma Radiation Oncology Group and Fondazione Italiana Linfomi Radiotherapy Committee [15,16].

INRT was delivered using conventional fractionation (2 Gy per fraction, five fractions per week). The prescribed dose was 20 Gy in 10 fractions for patients with early favorable disease and 30 Gy in 15 fractions for patients with early unfavorable disease. Patients experiencing a limited nodal relapse after chemotherapy alone could receive salvage INRT to the initially involved nodal sites and up to three additional nodal regions, with a total dose of 36 Gy in 18 fractions.

Target volume delineation followed the principles of the EORTC H10 trial and was based on pre-chemotherapy contrast-enhanced CT and FDG-PET/CT fused with the post-chemotherapy planning CT whenever feasible. The clinical target volume encompassed the initially involved nodal sites while accounting for tumor regression and respecting uninvolved normal tissues. CT-based simulation was mandatory.

Three-dimensional conformal radiotherapy and intensity-modulated radiotherapy, including volumetric techniques, were permitted. The choice of treatment technique was left to the treating radiation oncologist with the aim of achieving optimal target coverage while minimizing radiation exposure to organs at risk.

In summary, the planned treatment for LR groups 1a and 1b includes two or four chemotherapy cycles. In the case of limited relapse, INRT and nivolumab maintenance are given to both groups. In the HR group, the planned frontline treatment consists of a triple-modality regimen (four chemotherapy cycles followed by INRT and nivolumab). The extended relapse, defined as all other forms of disease relapse in the LR group or any relapse in the HR group, defines the failure of planned treatment and results in patient withdrawal from the study (Figure 2).

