### 2.4. Study Procedures

The recruitment period was planned from April 2021 to December 2023. Depending on risk stratification, patients undergo 18–49 visits, including the screening and the 12 follow-up visits (one every 3 months over the 36-month follow-up period).

At screening, the following data are collected: demographic and clinical characteristics; physical examination findings; disease-specific data (histological subtype, stage, number of involved nodal areas, extranodal involvement); patient breakdown according to mEORTC criteria; laboratory test results, Eastern Cooperative Oncology Group (ECOG) performance status; and functional test results, including pregnancy testing.

At treatment visits, the following data are collected: all changes in symptoms, physical examination, laboratory results; treatments administered; and adverse events. Pregnancy is verified at each treatment visit.

Collected information data during follow-up visits include date and extension of relapse in case of treatment failure; subsequent lymphoma treatment; secondary malignancies, cardio-vascular disease, and other organ toxicity; and survival.

Patients achieving complete metabolic response (CMR) on both PET-2 and end-of-treatment PET (EoT-PET) by blinded independent central review (see below) will undergo routine follow-up: clinical and laboratory evaluations every 3 months for the first 3 years, and additionally, a cfDNA assay (every 3 months during the first year, and every 6 months during the second year). PET imaging is performed only when indicated by clinical symptoms or laboratory abnormalities. If PET suggests HL relapse, a biopsy is strongly recommended to confirm the diagnosis of disease recurrence. Patients meeting criteria for limited relapse are included in group 2 and receive “delayed” INRT followed by nivolumab 240 mg every 14 days for 1 year.

Routine clinical data will be documented at study sites and entered into a secure, web-based electronic case report form (eCRF) system (The diCELLa eCRF Clinical Trials platform) (https://dicella.com/ecrf/ assessed on 14 August 2026). Documentation is sourced from routine medical records and verified for completeness through centralized and on-site monitoring by medical managers and clinical monitors. Imaging data and cfDNA are integrated with clinical data in the eCRF.

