The third secondary endpoint is 3-year overall survival (OS) of the entire cohort of patients enrolled into the study, defined as time from patient registration to death for any reason. The OS will be estimated using the Kaplan–Meier method, with a two-sided 95% CI based on Greenwood’s standard error.

As this is a single-arm evaluation, analyses of the secondary endpoints will be descriptive and will report point estimates with corresponding measures of precision, without formal hypothesis testing against a concurrent comparator. The summary of the study outcomes is presented in Table 1.

Finally, the diagnostic performance of cfDNA for detection of an impending relapse during follow-up in LR group patients will be summarized using overall accuracy, sensitivity, specificity, negative predictive value, and positive predictive value. Each metric will be presented as a point estimate with a two-sided 95% CI computed using the Clopper–Pearson exact method.

As an intention-to-treat (ITT) approach is preferred for phase III randomized clinical trials and a per protocol (PP) approach is preferred for equivalence and non-inferiority trials, a PP analysis will be preferred for assessing the primary study endpoint of treatment efficacy in LR patients, and an ITT approach will be used as secondary [30]. For all the other study endpoints in the RAFTING study, both an ITT and PP will be used.

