### 2.7. Missing Data Handling in the Analysis

In general, missing data will not be imputed for safety, demographic, or baseline characteristic variables; analyses will be based solely on observed data. For the primary endpoint and other time-to-event secondary endpoints, missing outcome information due to loss to follow-up or withdrawal of consent prior to an event will be addressed through right-censoring at the date of the last adequate disease assessment. These analyses assume that missingness is consistent with a missing at random (MAR) mechanism and that censoring is non-informative, such that the censoring process is independent of the event process conditional on the information available.

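### Withdrawing patients from the study at extended relapse conflicts with whole-cohort 3-year OS and with survival follow-up, and the last disease assessment is the wrong censoring date for OS

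*Protocol article*

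**What the plan says.** Section 2.3 (Patient Stratification and Treatment) describes extended relapse as "defined as all other forms of disease relapse in the LR group or any relapse in the HR group", and says that it "defines the failure of planned treatment and results in patient withdrawal from the study". No exception is made for survival follow-up.

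Section 2.6 names as third secondary endpoint the "3-year overall survival (OS) of the entire cohort of patients enrolled into the study", with death from any cause as the event. It adds: "The OS will be estimated using the Kaplan–Meier method, with a two-sided 95% CI based on Greenwood’s standard error". Table 1 repeats that the population is the entire cohort.

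Section 2.4 (Study Procedures) lists what is collected at follow-up visits: the date and extent of any relapse, then "subsequent lymphoma treatment; secondary malignancies, cardio-vascular disease, and other organ toxicity; and survival". It plans 12 visits over 36 months. The routine schedule it spells out is for patients in complete metabolic response on both PET-2 and the end-of-treatment PET. It does not say whether visits go on after a patient has been withdrawn.

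Section 2.7 sets one censoring rule "For the primary endpoint and other time-to-event secondary endpoints", so OS is covered. Outcomes missing because a patient is lost to follow-up or withdraws consent "will be addressed through right-censoring at the date of the last adequate disease assessment". The same section assumes that censoring is independent of the event process.

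**The concern.** OS on the entire cohort requires vital status to be followed after treatment failure. A site that takes Section 2.3 at its word stops following a patient at extended relapse and can no longer supply what Sections 2.4 and 2.6 need. The Kaplan–Meier estimate must then censor that patient at or near relapse. Relapse itself would cause the censoring, and it would remove from the risk set patients whose risk of death has just risen. The resulting error runs in one direction: OS is overstated.

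The second problem does not depend on how Section 2.3 is read. The last disease assessment suits endpoints for which progression is an event. For OS, a patient's status is known up to the last date on which the patient was known to be alive. Section 2.4 recommends PET in follow-up only when symptoms, findings or cfDNA call for it, so the last assessment that counts as adequate may fall well before the last contact. The known survival time in between is thrown away.

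OS is the only listed endpoint that counts deaths after treatment failure. The Discussion says that follow-up is still ongoing, so this can still be put right.

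**Working it through.** **The plan's own figure.** The only design figure that can be recomputed is the sample size. With expected rate 0.90, threshold 0.85, one-sided alpha 0.20 and power 0.80 (Section 2.5):

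n = p1(1 − p1)(z + z)² / (p1 − p0)² = 0.09 × (0.8416 + 0.8416)² / 0.05² = 101.999, so 102 low-risk patients.

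Total = 102 / 0.75 / 0.85 = 160.0.

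Both figures reproduce, and neither depends on the OS rules.

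**Which endpoints are exposed.** Extended relapse is itself an event for low-risk PFS, high-risk PFS, FF2TF and EFS (Section 2.6, Table 1). Leaving the study at that moment does not distort them. Only OS needs information from after it.

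**Size of the OS error under the literal reading.** The documents give neither the rate of extended relapse nor mortality after it. The inputs below are assumptions, with exponential times:

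- extended relapse by 3 years, r: 5%, 10% or 15% (8 to 24 of 160 patients)
- death within 2 years of extended relapse, d: 10%, 20% or 30%
- death without relapse by 3 years: 1%

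The yearly hazards are λ = −ln(1 − r)/3 for relapse, μ = −ln(0.99)/3 for death without relapse and δ = −ln(1 − d)/2 for death after relapse. Let S = exp(−3(λ + μ)) = (1 − r) × 0.99. Then:

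- deaths after relapse by 3 years = λ/(λ + μ) × (1 − S) − λ × (S − exp(−3δ))/(δ − λ − μ)
- deaths without relapse by 3 years = μ/(λ + μ) × (1 − S)

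Middle case (r = 10%, d = 20%): λ = 0.03512, μ = 0.00335, δ = 0.11157, S = 0.891.

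- Deaths after relapse: 0.09951 − 0.08430 = 0.0152
- Deaths without relapse: 0.0095
- 3-year OS with full follow-up: 1 − 0.0152 − 0.0095 = 97.5%

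If OS is censored at relapse, the Kaplan–Meier curve estimates only the death-without-relapse hazard, which gives 99.0% whatever r and d are. The overstatement is about 1.5 points.

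| r | d | OS, full follow-up | OS, censored at relapse | Overstatement (points) |
|---|---|---|---|---|
| 5% | 10% | 98.6% | 99.0% | 0.4 |
| 10% | 20% | 97.5% | 99.0% | 1.5 |
| 15% | 30% | 95.6% | 99.0% | 3.4 |

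A simulation of 400,000 patients per scenario gives the same results to within 0.05 points. Per 160 patients, full follow-up would count about 2.2 to 7.0 deaths, and the literal reading about 1.4 to 1.6.

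**If survival is collected after failure.** Patients stay in the risk set, their deaths are counted, and the overstatement is zero.

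**Censoring date.** The loss from using the last disease assessment depends on the gap between that date and last contact. The documents do not give this gap, so no size is put on it.

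**The case against.** The strongest reply is that nothing in the article says OS is censored at extended relapse. Section 2.7 names two triggers, being lost to follow-up and withdrawing consent, and a withdrawal directed by the protocol is neither. Section 2.4 lists later lymphoma treatment and survival as follow-up data. Since rescue of a limited relapse is part of planned treatment, later treatment most naturally means treatment after failure. The sentence in Section 2.3 closes a summary of planned treatment, so it may only mean that the patient comes off protocol treatment. The article also condenses a fuller protocol that may set this out.

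Much of this stands. A reader might infer that deaths after treatment failure are certain to drop out of OS. The documents do not support that, because the loss depends on the literal reading of Section 2.3. A reader might also want to state what share of deaths would be lost. The documents give no mortality after relapse. The Introduction's figure of 73% of relapses confined to initially involved regions does not give this trial's share of extended relapses either, because Section 2.3 lets a limited relapse include up to three new nodal sites.

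Two things remain. The conflict is between sentences that are in the article, so it is not a matter of omitted detail. If protocol-directed withdrawal falls outside Section 2.7, no stated rule covers it, and an estimate without later data would still have to censor at or near relapse. And Section 2.7 expressly includes OS in a rule tied to disease assessment.

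**Conclusion.** The point holds as a conflict between Section 2.3 and Sections 2.4 and 2.6, together with a censoring date in Section 2.7 that does not suit OS. Followed literally, Section 2.3 makes censoring of OS informative, against the plan's own assumption, and overstates 3-year OS by about 0.4 to 3.4 points under the assumed rates. If survival is collected after failure, this overstatement does not arise, and only the wording and the censoring date need repair.

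It would be tempting to treat this as a threat to the trial's main conclusion. It is not: OS is a descriptive secondary endpoint, and low-risk PFS, high-risk PFS, FF2TF and EFS are untouched by this mechanism. Nor does the article make OS its main check on de-escalation. That role falls to low-risk PFS, to EFS and to the interim rule on second relapses in Section 2.9. This should be fixed, but it does not put the primary analysis at risk.

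**What to change.** 1. Section 2.3: reconcile with Sections 2.4 and 2.6 by stating that extended relapse ends protocol treatment but not follow-up for survival.
2. Section 2.7: censor OS at the date last known alive. Keep the disease-assessment rule for PFS, FF2TF and EFS.
3. Confirm that vital status is held for every patient already withdrawn at extended relapse. Where it is not, and consent allows, obtain it.

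The cost is two clarifying sentences and a short vital-status query. Reported OS may come out slightly less favourable. The primary endpoint, its test and the sample size of 102/160 stay as they are.
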